### Sample size estimation

This RCT is a superiority trial, and an appropriate formula was used to estimate sample size [24]. Based on the results of our preliminary observational study and expert advice, we assume an α of 0.05, a 1 –β of 0.80, a between-group difference in primary outcome (total SQD scale score) δ of 8.0, a pooled standard deviation of 14.5, and an allowable dropout rate of 20%. The total sample size is expected to be 130 (65 in each group).

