## Statistical analysis

Data analysis will be performed with Stata v14.0 (StataCorp LLC, College Station, TX, USA). The main primary outcome analysis will be based on the intention-to-treat data set, where the missing values will not be imputed and the patients who took unscheduled medications will be kept in their original group. We will also perform four sets of sensitivity analyses to test the robustness of the results of the main analyses, including (1) using the per protocol data set; (2) imputing missing data using various methods dependent on the proportion and distribution of the missing data; (3) excluding patients who become aware of the grouping accidentally during the trial, which also aims to estimate the placebo effects; and (4) excluding patients who took unscheduled medications. The analysis of secondary outcomes will be based on the per protocol data set, and the analysis of safety outcomes will be based on the safety data set only, both with no imputation. Interim data analyses will be performed after weeks 8 and 52.

Descriptive analysis will be conducted to explore the means and standard deviations of the continuous variables. We will assess the treatment effects by comparing the mean between-group differences of the continuous endpoints with a normal distribution using the independent *t* test. The skewed continuous variables will be described using medians and interquartile ranges. We will use the Mann-Whitney *U* test to assess the equivalency of the skewed continuous variable distributions. Moreover, we will describe categorical variables through their frequencies and percentages. We will evaluate the between-group differences using Pearson’s chi-square test for the cases with expected counts greater than 5 in more than 20% of cells and greater than 1 in any cell or Fisher’s exact test otherwise. We will perform subgroup analyses stratified by gastric cancer stage and chemoradiotherapy regimen for the primary outcome. We set α = 0.05 as the nominal type I error rate, which will be adjusted for the multiple *t* test using the O’Brien-Fleming group sequential method [25].

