### Compliance and withdrawal

To improve patient compliance, we will offer all test samples (HGMX and placebo) and scheduled examinations free of charge, and patients will receive a travel allowance of 100 yuan at each visit. At the recruitment stage, researchers will emphasize the length of the 2-year treatment and follow-up to patients who are willing to join the trial. The patients will be allowed to complete each follow-up within ±3 days of the scheduled date for the weeks 2, 4, and 8 visits and within ±7 days for the weeks 26, 52, 78, and 104 visits. The used packaging bags will be reclaimed to check patients’ compliance.

Patients will be withdrawn from the trial for the following reasons:Cancer progression and restarting of radiotherapy or chemotherapyRecurrence of surgical complicationsContinuous deterioration of SQD symptomsPoor compliance, indicated by the use of less than 80% of the prescribed trial drug or more than two missed visitsActive withdrawal. Patients can actively withdraw from the trial at any time for any reason, and subsequent treatment will not be affected

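### The only stated comparison that fits adverse events uses crude percentages, which can be biased in either direction if withdrawal, and so observation time, differs between the arms.

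*Protocol article*

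**What the plan says.** Under Statistical analysis, the article sets the population and missing-data rule for safety: "the analysis of safety outcomes will be based on the safety data set only, both with no imputation". That sentence names no estimator. The next paragraph says "we will describe categorical variables through their frequencies and percentages", with between-group differences tested by Pearson's chi-square or Fisher's exact test. No person-time or time-to-event method appears anywhere in the article.

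Under Safety outcomes, the outcomes are AEs, severe AEs and withdrawal because of AEs. All three are naturally patient-level yes/no variables.

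Under Study visits and outcome assessments, follow-up is 2 years and self-reported AEs are recorded at each visit. Laboratory tests and electrocardiograms are done at weeks 8, 26, 52, 78 and 104.

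Under Compliance and withdrawal, the list opens "Patients will be withdrawn from the trial for the following reasons". It covers progression with restarted radiotherapy or chemotherapy, recurrent surgical complications, continuing worsening of spleen qi deficiency (SQD) symptoms, poor compliance (under 80% use or more than two missed visits), and the patient's own choice. Exit is from the trial, not only from the product, and no AE collection after exit is described.

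**The concern.** A crude percentage compares arms fairly only if both are observed for about the same time. Here several exits depend on things that treatment may change. SQD symptoms are the primary outcome, and progression enters a secondary outcome. Low use may follow from tolerability or taste, and the article says that product and placebo differ slightly in taste and smell.

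If Hou Gu Mi Xi (HGMX) works, more placebo patients may leave for worsening. HGMX patients then have longer in which to record an AE, and HGMX can show a higher percentage at the same true rate. If HGMX is less well tolerated and more of its patients leave, the bias runs the other way and part of a real excess can be hidden. Safety is a stated aim of the trial, so this comparison will carry weight.

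**Working it through.** **1. The plan's own figure.** Sample size estimation sets the type I error rate at 5% and power at 80%. The effect to be detected is "a between-group difference in primary outcome (total SQD scale score) δ of 8.0". The common standard deviation is taken as 14.5 points, and one patient in five may be lost. Sidedness is not stated. Taken as two-sided:

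n = 2 × (1.960 + 0.842)² × 14.5² / 8.0² = 51.6, so 52 per arm; 52 / 0.80 = 65 per arm, 130 in total.

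This matches the article. No figure is given for safety, and the 20% loss is not split by arm.

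**2. Model for the crude percentage.** These are my assumptions, as the article gives neither AE rates nor withdrawal by arm. AEs occur at constant rate a per year. Withdrawal occurs at constant rate w, unrelated to AE risk. AE recording ends at withdrawal, and T = 2 years. If a proportion W leaves by 2 years:

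- w = −ln(1 − W) / 2
- crude AE proportion = a / (a + w) × [1 − exp(−2(a + w))]

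**3. Equal true AE rates, 20% loss overall, a = 0.2 per year.**

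- W = 10%: w = 0.0527; 0.2/0.2527 × (1 − exp(−0.505)) = 0.7915 × 0.3967 = 31.4%
- W = 30%: w = 0.1783; 0.2/0.3783 × (1 − exp(−0.757)) = 0.5286 × 0.5308 = 28.1%
- W = 5%: w = 0.0256; 0.2/0.2256 × (1 − exp(−0.451)) = 0.8863 × 0.3632 = 32.2%
- W = 35%: w = 0.2154; 0.2/0.4154 × (1 − exp(−0.831)) = 0.4815 × 0.5643 = 27.2%

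Each pair below averages 20%. The true hazard ratio is 1.00 throughout.

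| Withdrawal, HGMX vs placebo | Mean years in trial | Crude risk ratio, a = 0.1 | a = 0.2 | a = 0.4 |
|---|---|---|---|---|
| 20% vs 20% | 1.79 vs 1.79 | 1.00 | 1.00 | 1.00 |
| 10% vs 30% | 1.90 vs 1.68 | 1.12 | 1.12 | 1.11 |
| 5% vs 35% | 1.95 vs 1.62 | 1.19 | 1.18 | 1.17 |

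Reversing the arms inverts the ratios: at a = 0.2, 1/1.12 = 0.89 and 1/1.18 = 0.85.

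**4. Chance of a false signal.** With 65 per arm, equal true hazards and a 2-year AE risk of 30% under full follow-up, the chance of a significant excess in the longer-observed arm is 5.8% at 10% vs 30% and 8.5% at 5% vs 35%. The nominal figure is 2.5%. At a 2-year risk of 50%, the chances are 7.9% and 12.9%.

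**5. The other direction.** Take a placebo 2-year AE risk of 30%, with 30% leaving HGMX and 10% leaving placebo. A true hazard ratio of 1.15 then gives equal crude percentages. A true hazard ratio of 2 still gives a crude risk ratio of 1.53 (43.8% vs 28.6%), but power falls to 44%, against 63% with 20% leaving each arm.

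**6. If AEs cluster early.** Assume 0.6 per year for 6 months and 0.05 after that, equal in both arms, with 10% vs 30% leaving. The crude risk ratio is 30.6% / 29.2% = 1.05. A patient-year rate ratio is 0.193 / 0.206 = 0.94, which errs the other way: the arm with longer follow-up adds mostly low-risk time. A time-to-first-event hazard ratio compares patients at the same time since randomization, so it stays at 1.00 in this setting.

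**The case against.** **The text is generic.** The safety sentence fixes only the analysis set, and the percentage sentence does not name AEs. The same section gives no method for progression-free survival, so it is not a full list of methods by outcome. Exposure-adjusted AE summaries are often left to an analysis plan, which is not shown here. This stands in part: the use of crude percentages for AEs is implied, not stated, and so is the end of AE recording at withdrawal. But it is the only stated method that fits these outcomes, and it sits badly with the article's own withdrawal rules.

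**There are safeguards.** A patient who leaves because of a recorded AE is already counted, and withdrawal because of AEs is a separate outcome. Some exits, such as recurrent complications, may themselves count as AEs. Severe AEs are reported within 24 hours, and the monitoring committee may stop the trial for a severe AE related to HGMX. This stands too. The masking risk is mainly for later AEs and for exits logged as low use or own choice.

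**A stronger reading does not hold.** A reader might infer that the plan makes an effective product look harmful, or a harmful one look safe. The article does not support that: bias needs unequal withdrawal, and a doubled hazard is weakened, not hidden. A reader might also take mean observed times of 1.9 and 1.5 years. At 0.2 per year these give (1 − exp(−0.38)) / (1 − exp(−0.30)) = 31.6% / 25.9% = 1.22. Under constant withdrawal, however, those times imply about 10% vs 45% leaving, or roughly 28% overall, above the planned 20%.

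**Conclusion.** The point holds in a limited form. The stated comparison ignores observation time, in a 2-year trial whose exit rules depend partly on outcome and compliance. If withdrawal differs by arm, the crude risk ratio can be off by about 11% to 19% within the planned overall loss, in either direction. The bias is smaller if AEs cluster early and nil if withdrawal is equal. That is enough to suggest a modest harm that does not exist or to hide one of similar size, but not to conceal a large one. The figures rest on assumed withdrawal splits and AE rates, a constant hazard, withdrawal unrelated to AE risk, and AE recording that ends at exit. The sample size is unaffected.

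**What to change.** Keep the percentages. For AEs and severe AEs, add a time-to-first-event comparison: Kaplan-Meier cumulative incidence by arm and a hazard ratio with 95% interval, censored at the end of AE observation. Report events per patient-year and time in trial by arm as description only, because the patient-year rate ratio is itself biased when AEs cluster early. State when AE observation ends for a patient who is withdrawn. The withdrawal rules need not change for this.

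The cost is a little more analysis and the date on which AE observation ended for each patient. The article does not say that this date is recorded, so the sponsor should confirm it. The added comparison still assumes that withdrawal is unrelated to AE risk, so it reduces the bias and does not guarantee its removal.

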### Outcome measurements

#### Primary outcome

The primary outcome is the change in the total score of the Spleen Qi Deficiency Symptoms Grading and Quantifying scale (SQD scale). The SQD scale is a modified version of the classic scale for assessing the degree of SQD in the Clinical Guideline of New Drugs for Traditional Chinese Medicine [21]. The SQD scale consists of 17 items regarding symptoms of SQD: (1) stomach distension, (2) abdominal distension, (3) physical fatigue and weakness, (4) mental fatigue and taciturnity, (5) loss of appetite, (6) abnormal stools, (7) stomach pain, (8) stomach tightness, (9) abdominal pain, (10) acid reflux, (11) belching, (12) nausea and vomiting, (13) abnormal bowel sounds, (14) powerless defecation, (15) sallow complexion, (16) loss of taste and hypodipsia, and (17) facial and limb edema. Items 1–6 are the main symptoms; the other items are secondary symptoms. The items are assessed for duration (0–3 points, only available for items 1–2 and 7–9), severity (0–3 points, not available for item 13), frequency per day (0–4 points; 0–3 points for item 5), and frequency per week (0–5 points). The total score is the sum of the scores of each item (the main symptoms are scored twice) and ranges from 0 to 292. A higher score indicates a more severe symptom. Compared with the classic scale, we added four items (items 1, 7, 10, and 11), defined the main symptoms according to TCM theory, and assessed each item for duration, severity, and frequency per day and per week rather than only for severity. The details of the SQD scale are presented in Additional file 1.

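### The primary analysis leaves the collected baseline SQD score unused and lets the observed distribution choose between a t test and Mann-Whitney; one baseline-adjusted mean difference would be more precise and fixed in advance

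*Protocol article*

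**What the plan says.** Under Primary outcome: "The primary outcome is the change in the total score of the Spleen Qi Deficiency Symptoms Grading and Quantifying scale (SQD scale"). Under Statistical analysis, treatment effects are assessed by "comparing the mean between-group differences of the continuous endpoints with a normal distribution using the independent" *t* test. Skewed continuous variables are summarised by median and interquartile range and compared by Mann-Whitney U, "to assess the equivalency of the skewed continuous variable distributions". No covariate is named for either test, and nothing says when a variable counts as skewed.

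Under Study visits and outcome assessments, there is a baseline visit and questionnaires are completed at every visit, so each patient should have a baseline SQD score.

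Sample size estimation assumes "a between-group difference in primary outcome (total SQD scale score) δ of 8.0" and "a pooled standard deviation of 14.5", with α 0.05, power 0.80 and 20% dropout, giving 130 patients (65 per group). It does not say whether 14.5 is the SD of the score or of its change, and it gives no correlation between baseline and follow-up.

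**The concern.** Two features of the stated method cost something.

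First, subtracting the baseline is not the same as adjusting for it. A raw change score gives the baseline a fixed coefficient of 1, whatever the true relation between baseline and follow-up. It therefore carries baseline noise into the comparison and responds to chance imbalance between arms at entry. A model with baseline as a covariate estimates that coefficient from the data.

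Second, the primary test depends on how the data look. The two tests do not address the same quantity: one compares means, the other compares distributions. The trial is sized on a mean difference of 8.0, which Mann-Whitney does not estimate. If the switch were made, the primary result would not be on the scale used for planning.

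The unclear basis of the SD matters as well. It decides whether the 80% power figure belongs to the planned test on change or only to a test on the follow-up score.

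**Working it through.** **1. The plan's own figure.** Inputs from Sample size estimation: δ = 8.0, SD = 14.5, α = 0.05 (taken as two-sided), power 0.80, dropout 20%.

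n per arm = 2 × (1.960 + 0.842)² × 14.5² / 8.0² = 51.6, rounded up to 52. Then 52 / (1 − 0.20) = 65 per arm, 130 in total. This matches the protocol. A one-sided α would need 41 per arm, or 104 in total after dropout, so two-sided is the reading that fits. Power at 52 completers per arm is 80.3% by the normal approximation and 79.6% by the noncentral t.

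**2. Variance formulas.** Let S be the SD of the score, assumed equal at baseline and follow-up, and ρ the correlation between the two. Neither the equality nor any ρ is in the protocol; ρ = 0.3, 0.5 and 0.7 is an assumed range.

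- Change score: variance 2(1 − ρ)S²
- Baseline-adjusted (ANCOVA): variance (1 − ρ²)S²
- Ratio, ANCOVA to change: (1 + ρ)/2 = 0.65, 0.75, 0.85, a reduction of 35%, 25%, 15%

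**3. If the SDs differ.** Let k be baseline SD divided by follow-up SD. In units of the follow-up variance, the change score has 1 + k² − 2ρk and ANCOVA has 1 − ρ². The difference is (k − ρ)², which is never negative but is zero when k = ρ. Example (assumed values): k = 0.6 and ρ = 0.6 give 1 + 0.36 − 0.72 = 0.64 and 1 − 0.36 = 0.64, so no gain. The 15% figure is therefore not a floor.

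**4. Power at 52 per arm, δ = 8.0, two-sided 0.05, noncentral t.**

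Reading A, 14.5 is the SD of the score. The SD of change is 14.5√(2(1 − ρ)); the ANCOVA residual SD is 14.5√(1 − ρ²).

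| ρ | SD of change | t test on change | ANCOVA SD | ANCOVA |
|---|---|---|---|---|
| 0.3 | 17.16 | 65% | 13.83 | 83% |
| 0.5 | 14.50 | 80% | 12.56 | 90% |
| 0.7 | 11.23 | 95% | 10.36 | 97% |

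Reading B, 14.5 is the SD of the change. The ANCOVA residual SD is 14.5√((1 + ρ)/2).

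| ρ | t test on change | ANCOVA SD | ANCOVA |
|---|---|---|---|
| 0.3 | 80% | 11.69 | 93% |
| 0.5 | 80% | 12.56 | 90% |
| 0.7 | 80% | 13.37 | 86% |

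These figures ignore the small cost of the O'Brien-Fleming adjustment and the one degree of freedom for the covariate.

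**The case against.** The unadjusted t test on change is unbiased and controls type I error in a randomised trial, so preferring ANCOVA is a recommendation about efficiency. That stands, and the point claims no more.

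A reader might infer that the power calculation was done on the wrong variable, the score instead of the change. The text does not support that. It speaks of the primary outcome and glosses it as the total score, while the primary outcome is defined elsewhere as the change. Either reading is possible. If 14.5 is the SD of change, the t test has its planned power. Even if it is the SD of the score, the t test falls short only when ρ is below about 0.5; at ρ = 0.7 it has 95%.

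A reader might also take 15–35% as an established gain. It rests on an assumed ρ and on equal SDs, and patients are selected for having symptoms at entry, so the baseline spread may well differ from that at follow-up.

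On the switch of test, the α adjustment refers to multiple t tests, which suggests that the t test is the intended main comparison. Skewness of a bounded score in patients expected to have mild symptoms also does not prove skewness of its change. Both remarks are fair. Still, the Mann-Whitney rule is written for continuous variables in general, without exempting the primary outcome.

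Finally, covariates and a normality criterion are often left to an analysis plan that is not shown. That would answer a complaint about silence. Here the article states the method, and the method it states makes no use of baseline and depends on the distribution.

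Adjustment for centre is weaker ground: Randomization and blinding describes no stratification by hospital, so omitting centre contradicts nothing.

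**Conclusion.** The point holds as a low-cost improvement in precision and pre-specification. It is not an error in the sample size, which reproduces, nor in the validity of the t test.

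The dependence of the primary test on the observed distribution needs no numerical assumption: it is in the text, and one of the two tests does not estimate the quantity on which the trial is sized.

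The size of the precision gain does rest on assumptions. It is 35%, 25% or 15% of the change-score variance at ρ = 0.3, 0.5 or 0.7 with equal SDs. It can be smaller if the SDs differ, but in large samples it is never negative. On Reading A, ANCOVA holds power at about the planned 80% or above for any ρ of zero or more (79.6% at ρ = 0), whereas the t test on change does so only from ρ of about 0.5. On Reading B, ANCOVA adds to a power that is already as planned. The recommendation is therefore the same on both readings, and the protocol should say which one applies.

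**What to change.** - Make the primary analysis a linear model of the follow-up SQD score on arm and baseline SQD score, with robust standard errors. Using change as the response gives the same treatment coefficient. Report the adjusted mean difference with 95% CI whatever the distribution. The model needs a named follow-up visit, as would a single t test.
- Keep Mann-Whitney U as a sensitivity analysis.
- Apply the same baseline adjustment to SF-36, body weight and body mass index.
- State in Sample size estimation whether 14.5 is the SD of the score or of the change and, if the preliminary study allows, the correlation between baseline and follow-up.
- Centre may be added as a covariate but need not be.

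The cost is wording: no new data, visits or patients, since the baseline questionnaire is already scheduled. The change should be made before outcome data are examined by arm, including at the planned interim analyses after weeks 8 and 52.

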### Data collection and monitoring

All investigators involved in the trial will receive research training based on standard operating procedures. An independent data monitoring committee (DMC) at Jiangxi University of Traditional Chinese Medicine will be founded and be responsible for supervising the entire trial process. Data collection, such as questionnaire surveys, physical examinations, biological samples, and laboratory examinations, will be performed by qualified physicians at each research center. Student volunteers, as clinical research coordinators, from Jiangxi University of Traditional Chinese Medicine will be in charge of contacting patients for timely follow-up. Each research hospital will have a clinical research associate from the Jiangxi University of Traditional Chinese Medicine who will be in charge of monitoring patient compliance and case report form completeness and will address issues during the trial. The original case report forms will be inputted into the online database by two clinical research coordinators in duplicate. Personal information for all patients will be anonymized. The database will be password protected and will be managed by the DMC. An independent analyst will have access to the database only during the data analysis period. The DMC will also have the authority to discontinue the entire trial according to the following standards: (1) HGMX does not show any efficacy toward SQD symptoms up to 8 weeks of follow-up, as indicated by an absolute difference < 5 on the SQD scale score between the two groups (this difference is estimated based on the unpublished results of our other trial assessing HGMX for nonorganic gastrointestinal disorders); (2) HGMX does not show statistically significant efficacy for any outcome up to 52 weeks of follow-up compared with placebo; and (3) any severe AE related to HGMX occurs.

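### The week-8 stopping criterion (difference below 5) would be met about 12-18% of the time if HGMX works as assumed, and the stated 80% power makes no allowance for it

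*Protocol article*

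**What the plan says.** Sample size estimation gives a fixed-design calculation. It sets the type I error at 0.05 and the power at 80%, and it plans for "a between-group difference in primary outcome (total SQD scale score) δ of 8.0". The SD is taken as 14.5 and dropout as 20%, which leads to 130 patients, 65 per arm. The section attaches the difference of 8.0 to no visit and does not mention early stopping.

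Statistical analysis plans interim analyses after weeks 8 and 52 and names O'Brien-Fleming for adjusting the type I error rate.

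Data collection and monitoring gives the DMC authority to end the trial on three grounds. The first is that HGMX shows no efficacy on SQD symptoms up to 8 weeks, "as indicated by an absolute difference < 5 on the SQD scale score between the two groups". The cut-off is said to come from unpublished results of another HGMX trial, in nonorganic gastrointestinal disorders. The second is that "HGMX does not show statistically significant efficacy for any outcome up to 52 weeks of follow-up compared with placebo". The third concerns severe adverse events and is not at issue here.

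For the first ground the article gives no number of patients at the look, no interval around the estimate and no direction of the difference.

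**The concern.** A cut-off of 5 lies close to the effect of 8 that the trial is built to detect. The standard error of the difference is about 2.5 to 3.2 points, so a product that works exactly as assumed can fall below 5 by chance. The criterion is described as showing no efficacy at all, yet a true benefit of 5 points would meet it half the time.

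An O'Brien-Fleming adjustment protects the type I error. It does not restore power lost to a futility stop. If the DMC uses the criterion, the trial can be abandoned when its own hypothesis is true, at a rate that the 80% does not reflect.

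There is also a wording problem. An absolute difference below 5 is, read literally, not met when HGMX is 5 or more points worse than placebo.

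**Working it through.** **Inputs from the article.** Difference 8.0, SD 14.5, α 0.05, power 0.80, dropout 20%, 65 per arm (Sample size estimation); 1:1 allocation (Randomization and blinding); cut-off 5 (Data collection and monitoring); 80 patients enrolled at submission, about 40 per arm (Trial status).

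**Assumptions.** The true week-8 difference equals 8 with SD 14.5. The look includes 65, 52 or 40 per arm. The week-8/final correlation within patients is 0.3-0.7. The final critical value is 1.96, or 2.004 as an O'Brien-Fleming bound for three looks.

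**1. The plan's own figure.** n per arm = 2(1.96 + 0.8416)² × (14.5/8)² = 51.6, so 52. Then 52/0.8 = 65 per arm, 130 in total. This reproduces the stated size exactly, two-sided and with no allowance for stopping. Power with 52 per arm is 80.3% (normal approximation).

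**2. Chance of meeting the criterion when the true difference is 8.** SE = 14.5 × √(2/n). The probability is Φ((5 − 8)/SE) − Φ((−5 − 8)/SE); the second term is negligible here.

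| Per arm at look | SE | (5 − 8)/SE | Criterion met |
|---|---|---|---|
| 65 | 2.543 | −1.18 | 11.9% |
| 52 | 2.844 | −1.05 | 14.6% |
| 40 | 3.242 | −0.93 | 17.7% |

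The result depends on the week-8 effect. With 52 and 65 per arm the criterion is met 24.1% and 21.6% of the time at a true difference of 7, 50% at 5, and 3.9% and 2.5% at 10.

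**3. Power if the criterion is always followed.** This is the bivariate normal probability that the week-8 difference is at least 5 and the final Z exceeds the critical value. The correlation of the two estimates is ρ × √(smaller n/larger n).

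| Week-8/final correlation ρ | 65 then 52 per arm, 1.96 | 65 then 52 per arm, 2.004 | 65 then 65 per arm, 1.96 |
|---|---|---|---|
| 0.3 | 72.4% | 71.4% | 79.1% |
| 0.5 | 73.8% | 72.8% | 80.4% |
| 0.7 | 75.4% | 74.4% | 82.1% |
| 0.9 | 77.5% | 76.5% | 84.6% |
| No futility rule | 80.3% | 79.1% | 88.2% |

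About 1 point of the shortfall in the 2.004 column comes from the O'Brien-Fleming bound (80.3% to 79.1%), not from the stopping criterion. With 52 per arm at both looks and a correlation of 1, the rule costs nothing (80.3%).

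**4. Direction.** If HGMX is truly 8 points worse, symmetry gives the same probabilities: read literally, the criterion is met only 11.9% (65 per arm) to 14.6% (52) of the time. A signed version would be met almost always.

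**5. No effect.** As written, the criterion is met with probability 2Φ(5/SE) − 1: 95% at 65 per arm, 92% at 52 and 88% at 40.

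**The case against.** The strongest reply is that the DMC may stop but need not. That stands: 12-18% is the chance of meeting a criterion, not of stopping. A reader might infer that the trial would be stopped that often and that 80% power is not delivered. The article does not support either as an unconditional statement. Still, it presents these grounds as standards for discontinuation, and its Discussion says that the early visits supply data for that decision, so the consequences of using the criterion matter.

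Second, much of the 12-18% overlaps with the 20% type II error already accepted. With 52 per arm an observed difference must reach 1.96 × 2.844 = 5.57 to be significant, so many trials below 5 at week 8 would have failed anyway. That is why power falls by about 5 to 8 points rather than 12 to 18. The loss shrinks as the correlation nears 1, and power stays near 80% if the planned dropout does not occur.

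Third, a reader might infer that the rule is meant to ignore harm. The documents do not support that. The lead-in speaks of HGMX showing no efficacy, which a worse result plainly satisfies, and an absolute difference may simply mean points rather than a relative change. What remains is an ambiguity in the only numerical indicator given.

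Fourth, it is tempting to put a false-pass rate on the week-52 ground. The article does not fix the tests, looks or correlations needed for one. At most, the words about any outcome let one nominally significant secondary result avoid stopping.

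**Conclusion.** The point holds as a conditional one. If the true week-8 difference is 8 with SD 14.5, the criterion is met about 12% of the time at 65 per arm and about 18% at 40. If the DMC acts on it, power is about 72-75% at a critical value of 1.96 (71-74% at 2.004) against 80.3% without the rule, given 65 per arm at week 8, 52 at the end and a correlation of 0.3-0.7. The look size, the correlation and the week-8 effect are assumptions, because the article states none of them. The 80% in Sample size estimation is a fixed-design figure with no stated allowance for the rule, and the criterion has no direction. Severity: should-fix. The size of 130 is correctly computed for the design that it describes.

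**What to change.** In Data collection and monitoring:

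- Define the difference as signed, placebo score minus HGMX score.
- State that the criterion is non-binding and how many patients the week-8 look includes.
- Consider tying the week-52 ground to the primary outcome.

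In Sample size estimation, restate the power with the rule included, or calibrate the cut-off so that the false-stop risk at a true difference of 8 is small. One option is to stop only if the upper 95% confidence limit for the week-8 benefit is below 8, that is, if the estimate is below 8 − 1.96 × SE (3.0 points at 65 per arm, 2.4 at 52, 1.6 at 40). The false-stop risk at a true difference of 8 is then 2.5%, and power is about 79-80% at 1.96 for 65 then 52 per arm and correlations of 0.3-0.7.

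The price of that option is fewer stops of an ineffective product: 88% at 65 per arm, 80% at 52 and 69% at 40, against 95%, 92% and 88% for the rule as written. Which boundary to use is a trade-off for the sponsor and the DMC. Stating the direction, the number at the look, the binding status and the resulting power needs only changes of wording in the protocol and DMC charter.
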